### Intervention

During the study period, the subjects maintained their original antidepressant type without any changes, and the dosage remained the same as before enrollment. For patients with severe insomnia, zolpidem tartrate tablets or zopiclone tablets can be taken before bedtime. The dose should not exceed the upper limit (maximum recommended dose) specified in the instructions. During the trial, participants will be allowed to use drugs for the treatment of somatic diseases in combination, and the type and dose of drugs will remain unchanged throughout the study.

### Active fMRI-rTMS group

The Black Dolphin Transcranial Magnetic Stimulation Robot (Spirit Dolphin, SLD-YXRJ-V1.0) is the medical device used for treatment, from Xi’an Solitai Brain Control Medical Technology Co. The stimulation site of transcranial magnetic stimulation is to precisely stimulate the right mPFC-amygdala functional junction. The stimulation parameters are a frequency of 10 Hz and an MT value of 120%. Each time, 50 treatment sequences were administered, consisting of 60 stimulations per sequence, with 30-s intervals between sequences, resulting in a total of 3000 stimulations per treatment. The treatment was administered once a day for 15 days.

### Sham fMRI-rTMS group

Rotate the coil so that it is 90° away from the scalp using the widely used sham stimulation technique. The appearance of the coil, stimulation frequency, stimulation time, and duration of the stimulation period are identical to those of the actual stimulation coil. Ineffective stimulation will result because the coil’s magnetic field cannot pass through the skull to produce current. The frequency of the treatments is the same as in the control group.

### Imaging acquisition

MRI scans were performed using a 3.0 T-UNITED Discovery 770 scanner equipped with a 32-channel head coil. Earplugs are used to reduce scanner noise. They are tight but comfortable enough to minimize head motion. T1-weighted sagittal anatomical images are obtained. The parameters were as follows: resolution = 1 mm × 1 mm; repetition time (TR) = 6.0 ms; echo time (TE) = 2.4 ms; slice thickness/gap = 1 mm; acquisition matrix = 256 × 256; magnetic field strength = 3 T; flip angle = 9°; and field of view (FOV) = 256 × 256 mm. Resting-state fMRI data are as follows: resolution = 3.5 mm × 3.5 mm; TR = 2000 ms; TE = 30.0 ms; slice thickness/gap = 4.0 mm; acquisition matrix = 64 × 64; magnetic field strength = 3 T; flip angle = 90°; FOV = 224 mm × 224 mm. During the scan, all participants are instructed to keep their eyes closed, relax, and refrain from thinking about anything in particular, while ensuring they do not fall asleep.

### Follow-up

Researchers will check in with the patients by administering clinical scales and evaluating their cognitive function assessment at the end of the 2nd, 4th, and 8th weeks after treatment. The researcher will contact the patient in advance via telephone to remind them of the significance of the follow-up evaluation to ensure that the visit is not missed. Follow-up depends on the situation. Try to come to the hospital for follow-up after negotiation with the subjects, or use the self-assessment scale for telephone follow-up.

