### Secondary outcome measure

Alterations in baseline scores on the seventeen-item Hamilton Depression Rating Scale, Montgomery-Asberg Depression Rating Scale, and other clinical scales will be used as secondary outcome measures both during treatment and at each follow-up point. The specific evaluation times were at baseline, at the end of treatment on day 7, at the end of treatment on day 15, 2 weeks after treatment, four weeks after treatment, and eight weeks after treatment.Seventeen-item Hamilton Depression Rating Scale (HAMD-17). HAMD is a widely used clinical tool for assessing the severity of depression [22]. The higher the total score, the worse the symptoms. The Chinese version of the 17-item Hamilton Depression Rating Scale demonstrated excellent interrater reliability, good item-total score correlations, and satisfactory internal reliability [23].Montgomery-Asberg Depression Rating Scale (MADRS). Each item is divided into 6 levels according to the identity level, with a score of 0–6 points. The total score of patients is 0–60. The higher the score of patients, the more severe the depression. The Chinese version exhibits high reliability, validity, and internal consistency. It is more sensitive in assessing efficacy than the HAMD [24].The Chinese Version of the Beck Scale for Suicide Ideation (BSI-CV). It is primarily used to identify individuals with suicidal tendencies and to assess the severity of suicidal thoughts. The assessment consists of 19 items, with each item offering 3 scoring options (0–2 points, respectively), resulting in a total score range of 0–38 points. A higher score indicates an elevated risk of suicide. The Chinese version exhibited high internal reliability and strong item-total correlations [25].Beck Depression Inventory (BDI). The self-rating scale is used to assess the severity of depressive symptoms. The assessment consists of 21 items, each divided into 4 levels of scores ranging from 0 to 3. The total score of the scale is the sum of the scores from all 21 entries. A higher total score indicates more severe symptoms of depression. The Chinese version demonstrates good reliability and validity in patients with depression [26].Insomnia Severity Index (ISI). The Chinese version of the ISI questionnaire has good reliability and validity in evaluating the perceived severity of insomnia [27]. The scale consists of 7 items, each scored from 0 to 3, resulting in a total score ranging from 0 to 28, with higher scores indicating poorer sleep quality.Clinical Global Impression (CGI). During each visit, the clinician evaluates the patient's overall condition, considering the severity of the illness, the patient's distress level, any other impairments, and the impact of the illness on functioning [28].Perceived Deficit Questionnaire for Depression (PDQ-D). The PDQ-D provides a subjective assessment of cognitive dysfunction. The Chinese version of the PDQ-D has been determined to be psychometrically valid for assessing subjective cognitive dysfunction in patients with depression [29]. The questionnaire comprises 20 questions, each scored from 0 to 4 points, with a total score ranging from 0 to 80 points. The higher the score, the more severe the cognitive impairment.The frequency and seriousness of adverse reactions, the occurrence of adverse events connected to the treatment, and the frequency of dropouts as a result of adverse reactions.Differences in brain imaging before and after therapy. Each patient underwent an MRI before and after treatment to determine the blood oxygen levels in each brain region. From this information, the functional connectivity between brain regions can be statistically determined, and the differences between the functional connectivity before and after treatment are then compared.

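### The telephone fallback at weeks 2, 4 and 8 covers only self-rated scales, so HAMD-17, MADRS, CGI and the cognitive test would be avoidably missing for patients who do not attend

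*Protocol article*

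**What the plan says.** The Follow-up section of the protocol article plans for researchers to be "administering clinical scales and evaluating their cognitive function assessment at the end of the 2nd, 4th, and 8th weeks after treatment". It then loosens this: "Follow-up depends on the situation". Two routes follow. One is a hospital visit: "Try to come to the hospital for follow-up after negotiation with the subjects". The other is to stay in contact remotely: "or use the self-assessment scale for telephone follow-up". No criterion is given for who takes which route.

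Under Secondary outcome measure, changes in HAMD-17, MADRS and the other clinical scales "will be used as secondary outcome measures both during treatment and at each follow-up point". For the CGI the same section says that "the clinician evaluates the patient's overall condition" at every visit. The BDI is described there as self-rated, and the ODQ is described as self-rated under Primary outcome measure. The legend to Fig. 2 names a cognitive function test.

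The Blinding section assigns follow-up evaluation to trained psychiatrists and keeps outcome assessors blind to allocation. The Statistical analysis section plans intention-to-treat analysis with multiple imputation, and repeated measures analysis of variance for the scales over treatment and follow-up.

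**The concern.** The only content named for a telephone contact is self-assessment. The outcome section requires instruments at the same time points that a patient does not complete alone. The two sections cannot both be met for a patient followed by telephone.

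Trial design gives the purpose of the post-treatment visits: to show how quickly the effect appears and how long it lasts. It names MADRS as the example of a secondary outcome. MADRS, HAMD-17 and CGI are the blinded clinician ratings on which that question partly rests, and the telephone rule drops them.

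Who attends is settled case by case after treatment, so the gaps may depend on the patient's condition. The loss comes from the rule itself: a psychiatrist is already assigned to do the follow-up evaluation, and the patient is already on the telephone.

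**Working it through.** **Which instruments survive a telephone contact, as the text stands**

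- ODQ (primary): self-rated, so it is kept.
- BDI: self-rated measure of depressive severity, so it is kept.
- ISI and PDQ-D: described as perceived or subjective measures, so probably kept.
- CGI: rated by the clinician at each visit, so it is lost.
- HAMD-17 and MADRS: lost. The article does not call them clinician-rated outright. This is inferred from the interrater reliability cited for HAMD-17, from the psychiatrist assessors, and from the absence of the self-rating label given to ODQ and BDI.
- Cognitive test: no telephone version is mentioned, so it is lost.

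Day 7 and day 15 are outside the telephone rule. The gap concerns weeks 2, 4 and 8 only.

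**Starting number per arm**

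The Sample size section gives ODQ 63 ± 23 against 80 ± 18, α = 0.05 and β = 0.1. The difference is 17 and the pooled SD is √((23² + 18²)/2) = 20.65. A two-sided two-sample t-test calculation gives 32.005, rounded up to 33 per arm, or 66 in total, which matches the stated figure. Then 66 × 1.2 = 79.2, taken up to 80, or 40 per arm. That calculation concerns the ODQ, which is not lost by this route, so the primary sample size is unaffected.

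**Loss of clinician-rated data**

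The documents give no telephone share p, so p is an assumption, taken as equal in both arms. Available number per arm = 40 × (1 − p). Standard error factor = √(1/(1 − p)).

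| p | number per arm | standard error factor |
|---|---|---|
| 20% | 40 × 0.8 = 32 | √(1/0.8) = 1.12 |
| 30% | 40 × 0.7 = 28 | √(1/0.7) = 1.20 |
| 40% | 40 × 0.6 = 24 | √(1/0.6) = 1.29 |

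The factor depends only on p, not on the starting number. If other dropout has already reduced the arms, the counts are smaller but the factor is the same.

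To put this in terms of power, assume a true difference of 0.5 SD on such a scale (not a figure in the article). With the normal approximation and two-sided α = 0.05, power is 61% at 40 per arm, 52% at 32, 46% at 28 and 41% at 24.

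All these figures are for observed ratings before imputation. Imputation that uses the ODQ and BDI from the same visit would recover part of the loss, by an amount that depends on how strongly they correlate with MADRS and HAMD-17. The article does not give that correlation.

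**The case against.** **The wording is loose.** The telephone sentence does not say that nothing else may be collected, and it does not forbid a psychiatrist from rating by telephone. The general requirement for clinical scales at weeks 2, 4 and 8 comes before it. This is fair, and it means that missing ratings are a consequence of following the rule as written, not a certainty. But self-assessment is the only content named for that route, and nothing in the article provides for remote clinician rating. The point therefore concerns a stated rule, not detail that a condensed article has left out.

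**The most important data are protected.** This stands. The fallback keeps the primary outcome for patients who might otherwise be lost. A reader might infer that durability of the effect on depression would rest on clinic attenders alone. The article does not support that, because the BDI measures depressive severity by self-rating and remains available.

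**There are mitigations.** Hospital attendance is the preferred route, patients are telephoned in advance, the sample was enlarged by 20%, and multiple imputation is planned. These reduce the problem. The imputation removes bias only if observed data explain who attends.

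**Bias between arms.** A reader might work out that, if non-attenders scored 5 to 10 MADRS points worse and the telephone share were 20% in one arm and 40% in the other, the difference would be biased by (0.40 − 0.20) × 5 to 10 = 1 to 2 points. The arithmetic is right, but neither input is in the documents. It also applies to an analysis of attenders only, which the article does not plan, and participants and assessors are meant to be blinded. With equal shares and an equal gap in both arms, this bias is zero.

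**Mode of the ODQ.** A reader might also infer that the ODQ is read aloud by telephone and that the mode goes unrecorded. Neither can be known: the article does not describe how the telephone scale is completed, and the case report form is not shown.

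**Conclusion.** The point holds for secondary outcomes. The Follow-up and Secondary outcome measure sections conflict for any patient followed by telephone. Under the rule as written, that patient has no HAMD-17, MADRS, CGI or cognitive result at the visit. The missingness is avoidable and may be related to the patient's condition.

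Its size depends on the unstated telephone share. Under the assumed range of 20% to 40%, 32 to 24 of 40 patients per arm would have clinician ratings, with standard errors about 12% to 29% larger before imputation. This assumes that HAMD-17 and MADRS are clinician-rated, which is well supported but inferred.

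The primary ODQ analysis and its sample size are not threatened by this route. Differential loss between arms is possible but is not shown by the documents. The change is worth making because it is cheap and preserves blinded ratings at the visits meant to show maintenance of effect.

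**What to change.** Amend the Follow-up section so that it agrees with Secondary outcome measure:

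- When a patient cannot attend, the same blinded psychiatrist rates MADRS, HAMD-17 and CGI by telephone or video within the visit window.
- The patient self-completes the ODQ and the other self-rated scales on the same form as in clinic, sent in advance or online.
- The mode of assessment is recorded for each visit.
- The cognitive test is stated to be collected only at hospital visits, so its absence after a telephone contact is expected and visible.

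In the analysis, include the ODQ and BDI from the same visit in the imputation model for the clinician-rated scales. Do not adjust the treatment comparison for mode. Mode is determined after randomisation and may depend on treatment and on outcome, so adjusting for it can itself introduce bias. Report the number of remote assessments by arm and visit.

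The cost is a short protocol amendment, one field on the case report form if it is not already there, and extra call time for existing raters. The downside is some added variability from remote rating. The article describes recruitment as ongoing, so follow-up visits still to come could benefit.

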### Ancillary and post trial care

In the event of damages related to this research, compensation or indemnification will be provided by Xijing Hospital following relevant national laws and regulations.

## Outcome measures

### Primary outcome measure

Our primary outcome will be the changes in ODQ scores [5]. It is a relatively new emotional blunting assessment tool for the self-rating scale, which consists of three parts and 26 questions, focusing on the patient's emotional experience over the previous week. The first part comprised 12 questions aimed at evaluating the subjects' current experience of emotional blunting. The second part consists of 8 questions designed to compare the patient's current state with their normal state before experiencing depression. The third part included 6 questions to gauge the extent to which patients believed their emotional blunting was linked to antidepressants, as well as whether these issues affected their treatment adherence. Each question is graded on a 5-point scale, ranging from 1 (disagree) to 5 (agree). The score and total score of each dimension were summarized (total score range: 26–130). The higher the value of ODQ is, the greater the degree of emotional blunting. The Chinese version of the ODQ has been validated to have good reliability [21].

### Secondary outcome measure

Alterations in baseline scores on the seventeen-item Hamilton Depression Rating Scale, Montgomery-Asberg Depression Rating Scale, and other clinical scales will be used as secondary outcome measures both during treatment and at each follow-up point. The specific evaluation times were at baseline, at the end of treatment on day 7, at the end of treatment on day 15, 2 weeks after treatment, four weeks after treatment, and eight weeks after treatment.Seventeen-item Hamilton Depression Rating Scale (HAMD-17). HAMD is a widely used clinical tool for assessing the severity of depression [22]. The higher the total score, the worse the symptoms. The Chinese version of the 17-item Hamilton Depression Rating Scale demonstrated excellent interrater reliability, good item-total score correlations, and satisfactory internal reliability [23].Montgomery-Asberg Depression Rating Scale (MADRS). Each item is divided into 6 levels according to the identity level, with a score of 0–6 points. The total score of patients is 0–60. The higher the score of patients, the more severe the depression. The Chinese version exhibits high reliability, validity, and internal consistency. It is more sensitive in assessing efficacy than the HAMD [24].The Chinese Version of the Beck Scale for Suicide Ideation (BSI-CV). It is primarily used to identify individuals with suicidal tendencies and to assess the severity of suicidal thoughts. The assessment consists of 19 items, with each item offering 3 scoring options (0–2 points, respectively), resulting in a total score range of 0–38 points. A higher score indicates an elevated risk of suicide. The Chinese version exhibited high internal reliability and strong item-total correlations [25].Beck Depression Inventory (BDI). The self-rating scale is used to assess the severity of depressive symptoms. The assessment consists of 21 items, each divided into 4 levels of scores ranging from 0 to 3. The total score of the scale is the sum of the scores from all 21 entries. A higher total score indicates more severe symptoms of depression. The Chinese version demonstrates good reliability and validity in patients with depression [26].Insomnia Severity Index (ISI). The Chinese version of the ISI questionnaire has good reliability and validity in evaluating the perceived severity of insomnia [27]. The scale consists of 7 items, each scored from 0 to 3, resulting in a total score ranging from 0 to 28, with higher scores indicating poorer sleep quality.Clinical Global Impression (CGI). During each visit, the clinician evaluates the patient's overall condition, considering the severity of the illness, the patient's distress level, any other impairments, and the impact of the illness on functioning [28].Perceived Deficit Questionnaire for Depression (PDQ-D). The PDQ-D provides a subjective assessment of cognitive dysfunction. The Chinese version of the PDQ-D has been determined to be psychometrically valid for assessing subjective cognitive dysfunction in patients with depression [29]. The questionnaire comprises 20 questions, each scored from 0 to 4 points, with a total score ranging from 0 to 80 points. The higher the score, the more severe the cognitive impairment.The frequency and seriousness of adverse reactions, the occurrence of adverse events connected to the treatment, and the frequency of dropouts as a result of adverse reactions.Differences in brain imaging before and after therapy. Each patient underwent an MRI before and after treatment to determine the blood oxygen levels in each brain region. From this information, the functional connectivity between brain regions can be statistically determined, and the differences between the functional connectivity before and after treatment are then compared.

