## Methods/design

### Objective

The primary objective is to explore the efficacy and safety of fMRI-rTMS precise stimulation of right mPFC-amygdala individualized targets in the treatment of depression patients with emotional blunting.The secondary objective is to analyze the neuroimaging mechanism that may be related to depressive emotional blunting symptoms by comparing the differences in imaging changes before and after fMRI-rTMS treatment in combination with clinical efficacy and to verify the mechanism of mPFC-amygdala functional connection in depressive emotional blunting symptoms.

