### Data monitoring: formal committee

To ensure the blinding, safety, and validity of the study, a Data Monitoring Committee (DMC) was established at the hospital. The committee consists of independent ethical, statistical, and clinical physicians and is independent of sponsors and competing interests. Any adverse reactions will be promptly reported to the DMC and relevant regulatory agencies.

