### Harms

Common adverse reactions include dizziness, headache, and tingling of the scalp. The main potential adverse reactions include seizures. As a result, all researchers involved in the study will receive training related to seizures before enrolling participants to ensure their safety. Any adverse reactions will be recorded in a paper CRF and reported immediately to the DMC and relevant regulatory agencies.

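### The harms outcome and the recording and reporting rules are worded for treatment-related events only, so other discrete events have no stated place in the comparison by arm

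*Protocol article*

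**What the plan says.** The Objective section puts safety beside efficacy: "The primary objective is to explore the efficacy and safety of fMRI-rTMS precise stimulation".

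The harms outcome is one item in the list under Secondary outcome measure. It opens with "The frequency and seriousness of adverse reactions" and continues with "the occurrence of adverse events connected to the treatment, and the frequency of dropouts as a result of adverse reactions".

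The Harms section gives the recording rule: "Any adverse reactions will be recorded in a paper CRF and reported immediately to the DMC and relevant regulatory agencies". The section on the formal data monitoring committee uses the same term: "Any adverse reactions will be promptly reported to the DMC and relevant regulatory agencies".

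Separately, the secondary outcomes include HAMD-17, MADRS, BDI, CGI and the Beck suicide ideation scale (BSI-CV). The first two and the "other clinical scales will be used as secondary outcome measures both during treatment and at each follow-up point". Of BSI-CV the article says: "It is primarily used to identify individuals with suicidal tendencies and to assess the severity of suicidal thoughts". The Data analysis section compares ODQ, MADRS, BSI-CV and other scores between groups by repeated measures analysis of variance.

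**The concern.** The purpose of a randomised sham arm, where safety is concerned, is that the difference in all-cause event frequency between arms shows what the treatment causes. Counting only events already considered treatment-related puts an individual opinion ahead of that comparison.

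Two things can go wrong. Events are discarded, which matters in a trial of 80, and an unexpected harm is the kind least likely to be recognised as related. The proportion attributed may also differ by arm if the person judging knows the allocation. Relatedness is an awkward idea in the sham arm anyway, because the article describes that stimulation as ineffective.

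No later analysis plan can repair this, since it cannot tabulate events that the case report form did not collect. The committee set up to protect safety also has no stated route by which it learns of a serious event considered unrelated. The stated trigger for immediate reporting is that something is a reaction, not that it is serious.

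**Working it through.** The point concerns a definition, and the plan has no harms figure to reproduce. The check sets the sections side by side and then shows, with assumed rates, how such a restriction acts.

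**Step 1. What each harms statement covers.**

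| Section | What is covered | Limit by cause |
|---|---|---|
| Secondary outcome measure, part 1 | frequency and seriousness | adverse reactions |
| Secondary outcome measure, part 2 | occurrence of adverse events | those connected to treatment |
| Secondary outcome measure, part 3 | dropouts | those due to adverse reactions |
| Harms | case report form, committee, regulators | adverse reactions |
| Data monitoring: formal committee | committee, regulators | adverse reactions |

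Part 2 is the clearest. It uses the general term, adverse events, and then narrows it explicitly. No section provides for recording, reporting or comparing adverse events regardless of cause.

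**Step 2. What reaches the arm comparison without attribution.** MADRS, HAMD-17 and BDI measure depressive worsening, CGI measures global worsening, and BSI-CV measures suicidal ideation. All are collected in both arms. The analysis is of scores, so it does not count individual events.

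**Step 3. What is left over.** Suicidal acts (BSI-CV covers thoughts and tendency), hospital admissions and medical events have no stated place unless they are called reactions. The same holds for discontinuation for a newly diagnosed psychiatric disorder. Withdrawal or dropout criteria lists that as a reason to end participation, but the outcome counts a dropout only if it is due to an adverse reaction.

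**Step 4. Who judges relatedness.** The article does not say. The treatment operator opens the allocation envelope (Implementation), outcome assessors are blinded (Blinding), and trained researchers collect the data (Data collection plan). None of these sections assigns the judgement to anyone.

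**Step 5. Illustration of lost events.** Arm size n = 40 is from the section on assignment of interventions. The true risks p (15% active, 5% sham) and the attributed proportion a are assumptions. Expected counted events = n × p × a.

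- a = 1: 40 × 0.15 = 6 and 40 × 0.05 = 2; difference 4.
- a = 0.5: 6 × 0.5 = 3 and 2 × 0.5 = 1; difference 2.
- a = 0.25: 6 × 0.25 = 1.5 and 2 × 0.25 = 0.5; difference 1.

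The ratio stays at 3 to 1 throughout. What shrinks is the count, and with it the information. If no event is counted in an arm of 40, the one-sided 95% upper bound is 1 − 0.05^(1/40) = 7.2%. That bound applies to attributed events and says nothing about the all-cause risk.

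**Step 6. Illustration of unequal attribution.** Assume a true risk of 30% in both arms.

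- Attribution 80% in both arms: 0.30 × 0.80 = 24% and 24%; no false difference.
- Attribution 80% active and 40% sham: 0.30 × 0.80 = 24% and 0.30 × 0.40 = 12%; a false difference of 12 points.

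The second case needs a judge who knows the arm, which the article neither states nor rules out.

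**The case against.** The strongest reply is that this is loose or translated wording in a condensed article. Withdrawal or dropout criteria speaks of adverse effects. The outcome lists reactions and then related events as if they were different things, which would be redundant if both meant attributed events. Definitions and serious-event procedures usually sit in the full protocol, and silence is not prohibition. The article also describes oversight that is not tied to attribution: ethics committee review of accumulated data, an annual ethics audit and steering meetings every 2 weeks.

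Part of this stands. The word only does not appear in the recording rule, and no causality procedure is described, so a deliberate filter cannot be asserted. But the article is not silent. It states the outcome, and one part restricts adverse events to those connected to treatment. The listed oversight does not say which events are recorded or compared.

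Four stronger readings are tempting, and the documents do not support them:

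- A reader might infer that clinical worsening and suicidality escape comparison altogether. They do not; Step 2 shows that worsening and ideation are measured in both arms and compared.
- A reader might infer that the unblinded operator attributes events and so biases the counts. No section says so.
- A reader might infer that a serious unrelated event will never reach the committee. The text shows only that no route is stated.
- A reader might infer that the safety objective cannot be answered. Related events, their seriousness, related dropouts and the psychiatric scales all bear on it, and the objective is only to explore safety.

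**Conclusion.** The concern holds as a stated restriction in the harms outcome, matched by the wording of the recording and reporting rules. Followed as written, it gives a weaker sham-controlled safety comparison than the trial could provide, although safety is part of the primary objective. It weakens that half of the objective without defeating it, because scale-based worsening and ideation remain compared between arms.

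The size is unknown. The figures in Steps 5 and 6 rest on assumed risks and attribution proportions and show direction only: fewer counted events if attribution is equal across arms, and a possible false difference if it is not. The conclusion assumes that the case report form follows the article's wording. If the full protocol already captures all adverse events, the remaining task is to bring the outcome definition into line with it.

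**What to change.** In Secondary outcome measure, Data monitoring: formal committee, and Harms, replace adverse reactions and treatment-connected events with all adverse events regardless of relationship, from the first session to week 8. Then:

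- ask about events in the same way in both arms at the contacts that already exist;
- record relatedness as a separate field, completed by a blinded assessor;
- send serious events to the Data Monitoring Committee whatever the attribution;
- tabulate all-cause events, serious events and discontinuations by arm, with related events as a subset.

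The cost is a change of wording and a case report form page. More minor unrelated events will be logged, and event rates will look higher in both arms. Trial status says that the first patient was recruited in February 2023, so capture before the change may be less complete than after it. The report should give the date of the change.
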